| 9. Subjects and numbers of subjects     | 
~ 1000 children 10-15 years of age for DENV and CHIKV seroprevalence study
 
~ 1000 parents of children from the seroprevalence study for a questionnaire study
 
~ 100 homes for mosquito sampling study
                                                                                                                                                                                                            |
| 10. Inclusion criteria                  | - Acceptance to participate                                                                                                                                                                                                                                                                                                                                                                                                           |
| 11. Exclusion criteria                  | - Refusal to participate or suffering from any concurrent infection or with any physical or mental disability.                                                                                                                                                                                                                                                                                                                        |
| 12. Material/ Biological samples        | 
- Finger-prick blood sample for use with Rapid Diagnostic Kit
 
- Adult mosquitoes
                                                                                                                                                                                                                                                                                                                                        |
| 13. Individual data collection and flow | 
For each participating child:
 
 
- information on age, sex and history of infection
 
- place of residence (longitude & latitude)
 
 
KAP questionnaire for parents/care givers – age, sex, address, education level
                                                                                                                                              |

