Dengue and chikungunya are associated with a wide range of socio-economic factors that alter the risk of exposure to infectious mosquitoes and which can vary at very local scales [1-8]. However, these associated risk factors are not systematic [9,10], likely influenced by the role of human mobility in ferrying the virus from places of high environmental risk throughout the city [11-13]. Indeed, low risk mosquito abundance areas do not necessarily lead to reduced exposure to virus and the key factor seems to be the extent of connectedness of an area. Analyses conducted in Bangkok have identified specific socio-economic factors associated with dengue cases, but whose association with dengue incidence radically alters and improves when factoring in the Bangkok transport matrix (connectivity among the 180 Khwaeng) and differs from when just using physical distance (Table 1). However, clinical dengue cases make up only a fraction of the true number of DENV infections and may be subject to reporting bias. A more robust measure of exposure is therefore using serology surveys across a wide range of age groups.

**Table 1.** Effect of matrices of distance and transport connectivity among subdistricts on association of SE variables with dengue cases in Bangkok. Shown are parameter estimates and percentage of variation explained in the multivariate statistical analyses.

|                  | Transport matrix |        | Distance matrix |        |
|------------------|------------------|--------|-----------------|--------|
|                  | w/o              | with   | w/o             | with   |
| No education     | 0.047            | 0.081  | 0.047           | 0.072  |
|                  | 2.2%             | 36.9%  | 2.1%            | 73.1%  |
| % Cement houses  | 0.0035           | 0.0045 | 0.0034          | -0.027 |
|                  | 11.5%            | 36.9%  | 10.8%           | 0.03%  |
| N° houses (100s) | 0.0023           | 0.0023 | 0.002           | 0.0036 |
|                  | 46.6%            | 18.9%  | 48.1%           | 23.3%  |

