## 9. STATISTICAL CONSIDERATIONS

Sample size:

Based on the preliminary data showing a difference in prevalence rates according to school centrality and environmental typology (approximately 26% vs 15%), we estimate a necessary sample size of ~210 children for each of the four typologies (Central+/Environmental+, Central+/Environmental-, Central-/Environmental+, Central-/Environmental-).

Sample size was calculated as follows [17]

$$n = (Z_{\alpha/2} + Z_{\beta})^2 \cdot [p_0(1 - p_0) + p_1(1 - p_1)] (p_0 - p_1)^2$$

Where n is the required sample size per treatment arm,  $Z_{\alpha}$  and  $Z_{\beta}$  are constants set by convention according to the accepted  $\alpha$  error and whether a one-sided or two-sided effect,  $p_0$  is the proportion sero-positive in area type 0 (ie Central + or Environment +), and  $p_1$  the proportion areas type 2 (Central – or Environment –).

Assuming a  $p < 0.05$  as acceptable and a study with 90% power, the following constant values are:  $Z_{\alpha/2} = 1.96$  and  $Z_{\beta} = 0.84$ .

Because our preliminary data indicated variation within school centrality and environmental typology, (coefficient of variation ranging from 0.6-1), we used the following formula to estimate the number of different sites for each typology.

$$\text{Site number per typology} = 1 + (Z_{\alpha/2} + Z_{\beta})^2 \cdot [p_0(1 - p_0)/n + p_1(1 - p_1)/n + k^2(p_0^2 + p_1^2)] (p_0 - p_1)^2$$

Where k is the coefficient of variation and n the number of individuals as calculated above. Using  $n=210$  and  $k=0.6$  to 1, we would need at least two and optimally three schools per environmental typology with 80-100 children per school.

Sero-positivity (as defined by the manufacturers instructions) will be analysed by logistic regression with age, sex and centrality (high vs. low) and environmental typology (Open vs Dense) as explanatory variables using R. School mosquito densities will also be included as an explanatory variable. In the subset of individuals collecting mosquitoes in the homes will be taken into account in a separate analysis. Mosquito densities will also be analysed with respect to the environmental typology and meteorological parameters.

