Socio-demographic and other baseline characteristic variables of a questionnaire will be reported descriptively using counts and percentage for categorical variables and means for continuous variables. Comparison of willingness to be vaccinated and other associated factors will be performed using one-way analysis of variance. Multivariate regression analysis will be deployed to identify and understand the key factors that may be associated with the potential uptake a vaccine using generalized linear models.

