### **10.2. Data confidentiality**

Once the RDT result and the grid level area of residence is established, the identification of the individual who provided the samples will no longer be possible. The identity of individual participants will be replaced with a code as follows:

Individual : XX-YYY-P/C

XX: School number

YYY: Individual number within the school

P/C: Parent or Child

Example: School 1, Individual 2, Child: 01-02-C

Correspondance between individual address and sample until geolocalisation enables environmental typology categorisation

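### Cheap improvement: report the seropositivity model with and without parental education, which is already collected, because the area types are not randomised and the model has no socio-economic term

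*Protocol*

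**What the plan says.** **The model.** Protocol section 9 states that sero-positivity "will be analysed by logistic regression with age, sex and centrality (high vs. low) and environmental typology (Open vs Dense) as explanatory variables". It continues: "School mosquito densities will also be included as an explanatory variable". No section adds a socio-economic term to this analysis.

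**The background.** Section 1 says: "Dengue and chikungunya are associated with a wide range of socio-economic factors that alter the risk of exposure to infectious mosquitoes". It adds: "Analyses conducted in Bangkok have identified specific socio-economic factors associated with dengue cases". It also qualifies this: "However, these associated risk factors are not systematic". It goes on to suggest that connectedness is the key factor.

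**The data.** Item 13 of the Summary lists: "KAP questionnaire for parents/care givers – age, sex, address, education level". About 1000 parents of the surveyed children are to answer. Section 10.2 gives each person a school number, an individual number within the school and a suffix ("P/C: Parent or Child"). Section 7.2 places the serology and questionnaire data in the same department.

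**The declared use.** Section 9 says: "Socio-demographic and other baseline characteristic variables of a questionnaire will be reported descriptively". The regression that follows there concerns vaccine uptake. The data table in section 7.2 gives description of the study population as the purpose of level of instruction.

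**The concern.** The primary objective is to find out how far connectedness and predicted mosquito abundance go with exposure, and the answer is meant to feed simulations of where to place vector control. The comparison is between kinds of place, with 2-3 schools each, and nothing balances the families across them. If family circumstances differ between area types and also relate to infection, part of a reported centrality or environment effect, or of its absence, could be social composition.

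The protocol raises this possibility in its own background and collects a variable that could test it. Section 9 nevertheless leaves that variable out of the model to which it is relevant.

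**Working it through.** **1. The planning contrast as yardstick.** Section 9 plans on 26% vs 15%. With its formula and constants: (1.96 + 0.84)² × (0.26×0.74 + 0.15×0.85) / 0.11² = 7.84 × 0.3199 / 0.0121 = 207, which agrees with the stated ~210 per typology. As an odds ratio the contrast is (0.26/0.74) / (0.15/0.85) = 0.3514 / 0.1765 = 1.99, with log 0.689. (The constant 0.84 belongs to 80% power, not the stated 90%. That is a separate matter and does not affect this point.)

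**2. What Table 1 shows for 'No education'.**

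| | Without matrix | With matrix |
|---|---|---|
| Transport: estimate | 0.047 | 0.081 |
| Transport: variation explained | 2.2% | 36.9% |
| Distance: estimate | 0.047 | 0.072 |
| Distance: variation explained | 2.1% | 73.1% |

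The education estimate depends on what spatial structure is in the model. Plain distance moves it almost as much as transport, so the shift is not specific to connectivity. The table covers subdistricts and reported dengue cases, an outcome that the same section says captures only a fraction of infections and may suffer reporting bias. It is a reason to adjust, not a child-level effect size.

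**3. Is a join feasible?** A parent code and a child code differ only in the last character, and one department holds both files. Erasing addresses does not remove the code. The protocol does not say that the records will be merged, so feasibility is an inference.

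**4. Possible size.** The documents give neither the effect of parental education on a child's serostatus nor its distribution by area. All inputs here except the two reference prevalences are assumptions.

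- No true area effect.
- Odds ratio of low parental education for seropositivity: 1.5, 2.0 or 2.5.
- Share of low education, reference vs other area: 30% vs 40%, 20% vs 40%, 20% vs 50%.
- Prevalence in the reference area: 15% (planning value) or 37.2% (pilot, ages 10-15).

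Let b be the prevalence with higher parental education and q the prevalence with low education, where q/(1−q) = OR × b/(1−b). Solve (1−s₀)b + s₀q = reference prevalence for b. The other area then has prevalence (1−s₁)b + s₁q.

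Example with OR 2.5, shares 20% vs 50% and reference 15%: b = 0.1227 and q = 0.2591. The other area has 0.5×0.1227 + 0.5×0.2591 = 0.1909. The false difference is 4.1 points, and the odds ratio is (0.1909/0.8091) / (0.15/0.85) = 1.34.

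| Shares | Reference 15%: points (OR) | Reference 37.2%: points (OR) |
|---|---|---|
| 30% vs 40% | 0.5-1.3 (1.04-1.10) | 1.0-2.2 (1.04-1.10) |
| 20% vs 40% | 1.1-2.7 (1.09-1.22) | 1.9-4.4 (1.09-1.20) |
| 20% vs 50% | 1.7-4.1 (1.13-1.34) | 2.9-6.7 (1.13-1.32) |

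Each range runs over odds ratios 1.5 to 2.5. On the log scale, the smallest and largest values are about 6% and 42% of the planning effect (0.042/0.689 and 0.290/0.689).

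**5. Wider assumptions.** With 15% prevalence in the higher-education group, odds ratios of 1.3 to 3, and shares from 30% vs 50% up to 20% vs 70%, the false difference runs from 0.7 to 9.8 points (odds ratio 1.06 to 1.73). The result is governed by the assumptions.

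**6. Direction.** The table shows a false positive effect only because it assumes no true effect and puts more low education in the area of interest. Reversing the shares reverses the sign.

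**The case against.** The strongest reply has four parts.

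- **The area association is the stated target.** Social composition may be part of what makes an area what it is, or may lie on the path to exposure, so an adjusted estimate answers a different question. This stands as a reason not to replace the unadjusted estimate. It does not argue against showing both.
- **The evidence is thin.** Table 1 is ecological and concerns reported cases. No section shows that one parent's education predicts a child's serostatus, and the larger artefacts need gaps of 20-30 points in low education that no section documents. This stands, and it limits the point to an improvement.
- **Adjustment will not settle the matter.** Education is one marker of social position. With 2-3 schools per typology and a planning coefficient of variation of 0.6-1 between sites, school-level differences remain. This also stands.
- **An analysis plan could add covariates.** It could, but the protocol names its adjustment set and assigns the education item another purpose.

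A reader might infer from Table 1 that low education is an established driver of dengue in Bangkok, so that any centrality effect found here is likely to be spurious. The documents do not support that. They speak of association, call the factors not systematic, and show education explaining only 2.1-2.2% without a matrix. If connectivity raises risk, the rise in the education estimate after adjustment would even suggest that low education and connectivity are inversely related. Omitting education would then pull the centrality estimate towards the null.

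**Conclusion.** The omission is certain; its consequence is not. The stated model has no socio-economic term, although the background gives a reason for one and a usable variable is collected. Because the area types are not randomised, the centrality and environment estimates could be biased in either direction. Under the main assumptions (education odds ratio 1.5-2.5, share gaps of 10-30 points, no true area effect), the artefact is an odds ratio of about 1.04 to 1.34, from negligible to roughly two fifths of the planning effect on the log scale. None of the education inputs comes from the documents.

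This is a cheap improvement, not a flaw that invalidates the study. The seroprevalence description is unaffected. It would be equally wrong to expect that adding education will separate place from social circumstances.

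**What to change.** In section 9:

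- State that parent and child records will be joined by the shared school and individual number.
- Report the centrality and environment estimates for dengue and for chikungunya both without and with parental education level as a covariate.
- Keep children without a returned questionnaire by multiple imputation of education.
- Do not adjust for the practice score from the questionnaire. Practice may be a consequence of past infection: the questionnaire study cited in the Background found better preventive practice among children with previous dengue (OR 1.34).

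In section 7.2, extend the declared purpose of level of instruction from description to adjustment of the seropositivity analysis, so that the two sections agree.

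**Cost.** No new data and no added burden on participants: a short addition to section 9, one file join, and a small change to the declared data use, which may need ethics notification. Some questionnaires will be missing. Residual school-level confounding should be acknowledged when the adjusted estimate is reported.

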| 2. Acronym                          | GeoMosquito                                                                                                                                                                                                                                                                                                                                                                                                                                                                                                                                                                                                                                                                                                 |
| 3. Type of study                    | 
A cross-sectional school-based seroprevalence study among children aged 10-15 years. Sero-conversion to dengue virus and chikungunya virus exposure will be measured by the Dengue IgG Rapid Diagnostic kit and the Chikungunya IgG Rapid Diagnostic kit, respectively.
 
A cross-sectional questionnaire study. Questionnaire about KAP about mosquito-borne diseases among their parents who enrolled in the seroprevalence study
 
A prospective observational study of mosquito sampling study in schools and in the homes of 10% of the recruited children using sticky traps
                                                                                                         |
| 4. Rationale                        | Specific places have the potential for being hotspots of viral transmission because of their conduciveness for mosquitoes and their environmental and demographic characteristics that enable these mosquitoes to find and bite their hosts. These areas are predicted to be responsible for the multiplication of cases at a hyperlocal level. Places that are hyper-connected (by transport networks) contribute significantly to viral spread at a city-wide scale, not least from the above-mentioned hotspots. We hypothesize that hyper-connected intra-urban districts will have a higher exposure to dengue and chikungunya, dependent upon the predicted environmental suitability for mosquitoes. |

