| 5. Principle objective              | Assess the extent of dengue virus and chikungunya virus seropositivity, using Rapid Diagnostic tests for IgG in ~1000 school children, aged 10-15 years of age, spread across 2-3 schools of four different environments classified by their degree of connectivity and extent of built-up area, is associated with highly connected areas and predicted high mosquito abundance areas within Bangkok.                                                                                                                                                                                                                                                                                                      |
| 6. Secondary objectives             | 
Collect mosquito samples in these 8-12 schools
 
Assess knowledge, attitude, and practice about mosquito-borne disease, control measures, and vaccine acceptance among parents
                                                                                                                                                                                                                                                                                                                                                                                                                                                                                                                  |
| 7. Principle criteria of evaluation | Seroprevalence rates                                                                                                                                                                                                                                                                                                                                                                                                                                                                                                                                                                                                                                                                                        |

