| 14. Study timeline                      | 
Estimated start date of enrollment: 01/06/2024
 
Enrollment period: 6 months
 
Duration of subject's participation:
 
 
- 4 months for mosquito sampling study
 
- 1 day for seroprevalence study and questionnaire
 
 
Total estimated study duration: 1 year
 
Data analysis: 6 months
 
Data storage period: 2 years after the last publication
 |
| 15. Number of centres                   | 8-12 schools                                                                                                                                                                                                                                                                                                                                                                                                                          |
| 16. Expected results                    | Sero-prevalence rates for dengue and chikungunya stratified by age, sex and environmental typology (4 types: High vs. Low centrality and High vs Low vegetation) of home and school. Mosquito abundance according to environmental typology. KAP on dengue and chikungunya.                                                                                                                                                           |

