As a pilot study, prior to roll-out across Bangkok, dengue virus sero-prevalence rates were measured using the Panbio Indirect IgG ELISA on stored blood samples from 272 children aged 3-15 years from within Bangkok. These were mapped according to their homes and schools, whose environmental typology (satellite imagery for vegetation index, height and surface of buildings) and degree of centrality (services density, frequency of transportation and visits using social media data) were established (see Figures below). The association of the degree of centrality (high vs. low) and the type of environment (Open vs. densely built-up) with sero-prevalence rates was then analysed by logistic regression, taking into account the ages of the individuals.

From this retrospective study, the median (IQR) age of the samples was 10.7 (7.6-12.6) years. DENV sero-prevalence rates among children 3-9 years and 10-15 years were 6.5% and 37.2% respectively. Children going to schools characterized by an open environment or one of low centrality had much lower sero-prevalence rates (Open vs. dense: 16.8% vs. 27.1%; Low vs high centrality: 14.8% vs. 25.2%). There was no difference in sero-prevalence rates according to the degree of centrality of their homes. However, sero-prevalence rates in homes in open environments were higher (27.1% vs. 12.6%) (Fig. 3).

**Figure 3.** Sero-prevalence rates according to landscape category and centrality in children's homes and schools

[figure not shown]

Suwanbamrung et al. [14] conducted a cross-sectional study among children aged 8-13 years from 50 public schools in Kanchanadit district to assess the correlation between knowledge, attitude and practice (KAP) in dengue infection including prevention method compare between children with and without dengue infection experience using 32-items questionnaire. The study shows no significant difference in KAP mean score between the 2 groups, but the children with previous dengue infection had better preventive practice than the other group (OR 1.34, 95%CI 1.03-1.75,  $P=0.032$ ). The study also notes that most children (more than 70%) reported that their source of dengue information came from their teacher. Thus, in addition to the sero-prevalence study, we are also interested in assessing levels of KAP concerning dengue and provide more information about dengue infection and prevention, which can then be applied in their school and household.

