## 2. **OBJECTIVES**

### **Primary objective:**

To address the extent to which (satellite-) predicted and empirically validated mosquito abundance and mapped transport/mobility connectedness among Khwaeng do associate with DENV and CHIKV exposure as measured by sero-positivity. Coupled with a detailed geographic information system (GIS) of Bangkok, including fine scale meteorological data, will subsequently enable fine scale agent-based simulation models to test *in silico* the efficacy of implementing vector control in a variety of locations.

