### **3.2. Evaluation criteria**

#### **Principle evaluation criteria:**

Epidemiological read-out – sero-prevalence

To assess the association of centrality with exposure to DENV and CHIKV, we will perform a sero-prevalence study using Rapid Diagnostic kits on children 10-15 years spread across 8-12 schools in Bangkok.

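### The seropositivity model leaves home and school typology unseparated, names no centrality-by-environment term, and is stated only with mosquito density in it

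*Protocol*

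**What the plan says.** **Model.** Section 9 lists age, sex, centrality (two levels) and environmental typology (two levels) as explanatory variables in a logistic regression, and continues: "School mosquito densities will also be included as an explanatory variable". It does not say whether the typology is that of the home or the school, and it names no product term. The homes with traps get a separate analysis, for which no model is given. The same paragraph then plans to analyse mosquito density itself against environmental typology.

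**Hypothesis.** The Rationale (Summary, item 4) reads: "We hypothesize that hyper-connected intra-urban districts will have a higher exposure to dengue and chikungunya, dependent upon the predicted environmental suitability for mosquitoes".

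**Objectives.** Summary item 5 asks whether seropositivity "is associated with highly connected areas and predicted high mosquito abundance areas within Bangkok". The primary objective in Section 2 asks how far "predicted and empirically validated mosquito abundance and mapped transport/mobility connectedness among Khwaeng do associate with DENV and CHIKV exposure". Section 3.2 states the principal criterion as: "To assess the association of centrality with exposure to DENV and CHIKV".

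**Home and school.** Summary item 16 promises seroprevalence by "environmental typology (4 types: High vs. Low centrality and High vs Low vegetation) of home and school". Section 7.1 collects coordinates of both places and classifies them into the four types. The Background reports the pilot by school and by home. Dense schools had the higher rate, but for homes "sero-prevalence rates in homes in open environments were higher (27.1% vs. 12.6" per cent. Centrality made a difference at school and none at home.

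**The concern.** Section 9 does more than leave detail open: it lists the terms of the model, and three features of that list do not fit the rest of the protocol.

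1. **Whose typology.** In the pilot, the sign of the environment contrast and the presence of a centrality contrast both depended on whether the place was the school or the home. With one term for each factor, the result turns on an undefined choice. If school is meant, home typology drops out of the regression although it is collected and reported on.
2. **The conditional hypothesis.** Without a product term, the model imposes the same centrality odds ratio in both environments. It cannot show the dependence that the Rationale predicts.
3. **Density in the only stated model.** The protocol treats density partly as a consequence of environment. An environment coefficient adjusted for density is what remains after the mosquito pathway is held fixed. The total association of environment with seropositivity is not given by any stated model.

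At stake is whether the reported coefficients answer the questions the study was set up to ask, and whether home or school terms are chosen only after the data are seen.

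**Working it through.** **The plan's own figure.** Inputs from Section 9: p0 = 0.26, p1 = 0.15, constants 1.96 and 0.84.

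n = (1.96 + 0.84)² × [0.26×0.74 + 0.15×0.85] / (0.11)² = 7.84 × 0.3199 / 0.0121 = 207.3.

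This reproduces the stated figure of about 210 per typology. The constant 0.84 belongs to 80% power, not the stated 90%; that is a separate matter. What counts here is that p0 and p1 contrast one factor at a time, so the sample size targets an average effect and not a product term.

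**(1) Home versus school.** Crude pilot percentages from the Background, reading the comparator for open homes as dense homes:

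| Contrast | School | Home |
|---|---|---|
| Environment, dense minus open | 27.1 - 16.8 = +10.3 points | 12.6 - 27.1 = -14.5 points |
| Centrality, high minus low | 25.2 - 14.8 = +10.4 points | reported as no difference |

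A single environment term would therefore be expected to have opposite signs under the two readings.

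**(2) No product term.** Assumed pattern for illustration: 26% in one of the four cells and 15% in the other three, so that centrality acts in only one environment.

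- True centrality odds ratios: (0.26/0.74)/(0.15/0.85) = 1.99 in one environment and 1.00 in the other.
- Additive logistic model fitted to these four equal cells: centrality odds ratio 1.46 in both environments.
- With the product term: interaction odds ratio 1.99, log odds ratio 0.689.

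Precision of that term, ignoring clustering: SE = √Σ 1/[n p(1-p)] over the four cells.

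- n = 210: SE = √(1/40.40 + 3/26.78) = 0.370; power = Φ(0.689/0.370 - 1.96) = 46%.
- n = 250 (1000/4): SE = 0.339; power = 53%.
- For 80% power: about 476 per cell. For 90%: about 637.

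**(3) Density in the model.** Simulation with 12 schools of 84 children, 300 runs per row. Assumptions: density equals the environment indicator plus normal noise with SD 0.5; a share m of an environment log odds ratio of 0.689 runs through density; there is no other variation between schools.

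| Share m through density | OR without density | OR with density | SE of log OR, without | SE of log OR, with |
|---|---|---|---|---|
| 0% | 2.00 | 2.05 | 0.15 | 0.26 |
| 25% | 2.04 | 1.68 | 0.17 | 0.28 |
| 50% | 1.98 | 1.42 | 0.19 | 0.26 |
| 75% | 2.01 | 1.16 | 0.21 | 0.27 |
| 100% | 1.98 | 1.01 | 0.26 | 0.27 |

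The protocol gives no value for m, so the table shows a range and not an expected loss.

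**The case against.** **The additive model answers the stated criterion.** Section 3.2 asks about the association of centrality with exposure, Summary item 5 asks about connected areas and high-abundance areas, and the sample size contrasts one factor at a time. An average association serves all of these. This stands. A reader might infer that the model cannot test the study hypothesis at all; the documents support only that it cannot show how the centrality association varies with environment.

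**Density belongs in a model.** Section 2 makes mosquito abundance an exposure of primary interest, so including it is not an error. This also stands. A reader might infer that adjustment wipes out the environment effect. That would need the whole effect to pass through density, which the documents do not say. Nor do they place density on the pathway from centrality: the Background stresses connectedness as distinct from abundance. What remains is that no model without density is stated.

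**Section 9 is a list, not a closed formula.** Product terms and coding are often left to an analysis plan, which is not shown, and item 16 promises descriptive rates by all four types for home and school. Descriptive rates do help. But they are not adjusted jointly for the other place, and the listed terms do not reflect the Rationale or the pilot.

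**Sizing the home-school confounding.** It is tempting to combine +10.3 and -14.5 with a guessed proportion of children whose home and school types agree, and to quote a percentage of the school effect that would be hidden. The documents do not support this. They give no such proportion, and each crude contrast already carries some of the other place's effect. The percentages also come from 272 children aged 3-15, whose seroprevalence was 6.5% at 3-9 years and 37.2% at 10-15, and they are not shown as age-adjusted.

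**Conclusion.** The point holds as a mismatch between the stated model and the protocol's own aims. The strongest part is home versus school: the data are collected, results are promised for both, and the pilot contrasts differ in sign for environment and in presence for centrality. The missing product term means the conditional part of the hypothesis is not estimated; the figures (1.99 and 1.00 both reported as 1.46) rest on the assumed 26/15/15/15% pattern. The density part is narrower: the total environment association lacks a stated model, and the size of the difference depends on an unknown mediated share.

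Nothing here shows that the average centrality association is unobtainable, or that a specific fraction of any effect would be lost. A shortage of school-level degrees of freedom is not an argument against density either, because the product term recommended below uses one as well.

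**What to change.** State in Section 9:

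1. A model for total typology associations: age, sex, school centrality, school environment, home centrality and home environment, without mosquito density.
2. The product of school centrality and school environment added to it, with the centrality contrast reported within each environment as an estimate with an interval, not as a pass-or-fail test.
3. A second model that adds school mosquito density, for the abundance objective in Section 2.

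This changes wording only; every variable is already collected. Both typologies must be linked to each child before the coordinates are erased, as Section 7.2 already provides.

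The price is precision. The product term has about 46-53% power under the assumed pattern before clustering. School-level information is thin: an intercept and three school-level terms leave 12 - 4 = 8 degrees of freedom with 12 schools and 8 - 4 = 4 with 8 schools. Adding density leaves 7 and 3. The protocol should say so and treat the product term as estimation.
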